### Procedure

2.2

For this cross-sctional and interventional study all MDs of the SAF will be contacted via the secure e-mail system of the SAF electronic platform. The invitation e-mail will explain the study aims, the approval process, the voluntary nature of participation, and the coded data handling. Further, participants will be informed that participation or non-participation will have no advantages or disadvantages for their professional and military career. The study will be conducted according to the seventh and current version (115) of the Declaration of Helsinki, and the study has been approved on March 28, 2024 by the local ethics committee (EKNZ; Ethikkommission Nordwest- und Zentralschweiz; Basel, Switzerland: register code: 2024–00258).

### Survey-study 1; study design

2.3

Participants who provide written informed consent will receive a survey link (see Table 1 for a description of the study measures). The baseline survey data will be analyzed to get a descriptive overview, including prevalence rates of participants’ sleep disturbances and psychological well-being. Next, those MDs with sleep disturbances along with issues of psychological well-being will be identified and are eligible for the Intervention-Study 2.

**Table 1 tab1:** Overview of the questionnaires.

Survey		
Dimension	Measure	Reference
Sociodemographic and military-related information	Self-administered questionnaire	
Sleep		
Insomnia	Insomnia Severity Index (ISI)	Gerber et al. (116) and Bastien et al. (117)
Sleep continuity	Pittsburgh Sleep Quality Index (PSQI; modified)	Buysse et al. (118)
		
Physical activity	International Physical Activity Questionnaire (IPAQ); short form	Craig et al. (119) and Lee et al. (120)
Psychological well-being		
Depression	Patient Health Questionnaire (PHQ-9)	Kroenke et al. (121)
Coping strategies	Stressverarbeitungsfragebogen [Coping with stress questionnaire]; short form	Erdmann and Janke (122)
Depression, anxiety, stress	Depression, anxiety, stress questionnaire (DASS-21)	Lovibond and Lovibond (123, 124)
Emotion regulation	Emotion Regulation Questionnaire	Gross and John (125)
Concentration	Adult Concentration Inventory	Fredrick et al. (126) and Sadeghi-Bahmani et al. (127)
Social activity	Social Adaptation Self-evaluation Scale (SASS)	Bech et al. (128)
Strengths and Difficulties	Strengths and Difficulties Questionnaire (SDQ); adult version	Goodman (129)
Mental toughness	Mental toughness Questionnaire; short-form, 18	Dagnall et al. (130)

Intervention					
Dimension	Measure	Reference		Time points	
			Baseline	Week 3	Week 6 (stud end)
Sociodemographic and military-related information	Self-administered questionnaire		X		
Sleep					
Insomnia	Insomnia Severity Index (ISI)	Bastien et al. (117) and Gerber et al. (116)	X	X	X
Sleep continuity	Pittsburgh Sleep Quality Index (PSQI; modified)	Buysse et al. (118)	X	X	X
Sleep-related cognitions and emotions					
**Dysfunctional beliefs and attitudes about sleep**	Dysfunctional beliefs and attitudes about sleep	Morin et al. (131)	X	X	X
**Pre-sleep cognitions and emotions, including bed time procrastination**	Bedtime Procrastination Scale (BPS)	Kroese et al. (132) and Kroese et al. (133)	X	X	X
					
Physical activity	International Physical Activity Questionnaire (IPAQ); short form	Craig et al. (119) and Lee et al. (120)	X		X
Psychological well-being					
Depression	Patient Health Questionnaire (PHQ-9)	Kroenke et al. (121)	X	X	X
Coping strategies	Stressverarbeitungsfragebogen [Coping with stress questionnaire]; short form	Erdmann and Janke (122)	X		X
Depression, anxiety, stress	Depression, anxiety, stress questionnaire (DASS-21)	Lovibond and Lovibond (123, 124)	X	X	X
Emotion regulation	Emotion Regulation Questionnaire	Gross and John (125)	X		X
Concentration	Adult Concentration Inventory	Fredrick et al. (126) and Sadeghi-Bahmani et al. (127)	X		X
Social activity	Social Adaptation Self-evaluation Scale (SASS)	Bech et al. (128)	X		X
Strengths and Difficulties	Strengths and Difficulties Questionnaire (SDQ); adult version	Goodman (129)	X		X
Mental toughness	Mental toughness Questionnaire; short-form, 18	Dagnall et al. (130)	X		X
**Experiential avoidance**	Experiential Avoidance Scale	Hayes et al. (134) and Zakiei et al. (99)	X	X	X
**Mindfulness self-awareness**	Freiburg Mindfulness Inventory (FMI)	Walach et al. (135)	X	X	X

Information in bold characters = additional questionnaires for the intervention study. X = completing the questionnaires.

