**Method:**

All MDs serving in the SAF (*N* = 480) will be contacted via the SAF-secured communication system to participate in a cross-sectional survey of sleep disturbances and psychological well-being (‘Survey-Study 1’). Those who consent will be provided a link to a secure online survey that assesses sleep disturbances and psychological well-being (depression, anxiety, stress, coping), including current working conditions, job-related quality of life, mental toughness, social context, family/couple functioning, substance use, and physical activity patterns. Baseline data will be screened to identify those MDs who report sleep disturbances (insomnia severity index >8); they will be re-contacted, consented, and randomly assigned either to the eCBTi or the active control condition (ACC) (‘Intervention-Study 2’). Individuals in the intervention condition will participate in an online standardized and evidence-based group intervention program of cognitive behavioral therapy for insomnia (eCBTi; once the week for six consecutive weeks; 60–70 min duration/session). Participants in the ACC will participate in an online group counseling (once the week for six consecutive weeks; 60–70 min duration/session), though, the ACC is not intended as a *bona fide* psychotherapeutic intervention. At the beginning of the intervention (baseline), at week 3, and at week 6 (post-intervention) participants complete a series of self-rating questionnaires as for the Survey-Study 1, though with additional questionnaires covering sleep-related cognitions, experiential avoidance, and dimensions of self-awareness.

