#### Measures for the eCBTi intervention and active control condition

2.5.2

The following questionnaires will be identical in both the initial survey and the intervention study: Sociodemographic and military-related information, sleep, physical activity, depression, coping strategies, depression, anxiety and stress, emotion regulation, social activity, strengths and difficulties, mental toughness (see Table 1).

In addition to the above mentioned questionnaires, the intervention study will also assess several additional psychological constructs with the following surveys:

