### Sample size calculations

2.7

To calculate the sample size for the intervention study, we used the G*Power software (143). Based on previous studies on the efficacy of eCBTi (86–92), we expect a partial eta-squared of 0.08 (medium effect); alpha: 0.05; Power: 0.95; number of groups: 2; number of measurements: 3; total sample size: 32, that is, 16 per condition. To counterbalance possible drop-out, we assess 25 participants per condition.

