#### Intervention

2.8.1

ANOVAs for repeated measures are run with the factors Group (eCBTi vs. ACC), Time (baseline, week 3, week 6), and the Group x Time-interaction; dependent variables as reported in Table 2. Post-hoc analyses after Bonferroni-Holm are used for p-corrections for multiple testing. Single mean comparisons are performed with Cohen’s d effect sizes, as proposed by Becker (149). In case of missing values, such missing data will be replaced with the means or medians of the sample (144, 145, 150, 151). For the intervention study: Statistical procedures are run both by protocol (that is: only available data observed at any time point from every participant are considered) and by intent-to-treat (ITT) with the last intervention carried forward (LOCF) (152). Further, we consider the following confounders, that is to say, we statistically calculate, whether the pattern of results might get biased in the same or opposite directions for the following confounders: Age, gender, working condition, including current full time or part time positions as medical doctors, including their subspeciality such as neurosurgeon, anesthesiologist, or emergency MD, to name but a few, and military rank, or time lapse between the assessment and the last deployment.

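### Randomised doctors' pre-randomisation survey scores are not used in the Intervention-Study 2 analysis; adjusting for them would be an optional, modest gain in precision

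*Protocol article*

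**What the plan says.** Entry to the trial runs through the survey. Respondents with an ISI above 8 are identified, and "they will be re-contacted, consented, and randomly assigned either to the eCBTi or the active control condition" (Abstract, Method). The trial then has its own baseline: "At the beginning of the intervention (baseline), at week 3, and at week 6 (post-intervention) participants complete a series of self-rating questionnaires". These are two separate administrations. Table 3 puts the survey link in July/August and the groups from September 2024 to February 2025.

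The scales overlap. Section 2.5.2 introduces its list with "The following questionnaires will be identical in both the initial survey and the intervention study", and Table 1 shows the ISI, the modified PSQI and the shared well-being scales in both parts. Four scales are added only for the trial: sleep beliefs, bedtime procrastination, experiential avoidance and mindfulness.

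Section 2.3 gives the use of the survey data as description ("The baseline survey data will be analyzed to get a descriptive overview") and identification of eligible doctors; section 2.8 adds associations within the survey. Section 2.8.1 analyses the trial by repeated-measures ANOVA with Group, "Time (baseline, week 3, week 6), and the Group x Time-interaction". Its confounder list covers age, gender, working condition and subspeciality, military rank and time since last deployment. The survey score of the outcome is not on it.

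**The concern.** An earlier measurement of the same scale is often a better predictor of a later score than age, gender or rank. Here it exists for everyone randomised, it can be linked because the data are coded with a stored key (section 2.10), and it predates randomisation, so adjusting for it cannot bias the comparison between arms. Two pre-treatment scores can average out more short-term noise than one.

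Only precision is at stake. It has some value here: the plan is for 50 doctors from a pool of 480, and section 3.2 concedes that participation is uncertain, so further recruits may not be available.

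**Working it through.** **The plan's own figure.** Section 2.7 gives "we expect a partial eta-squared of 0.08 (medium effect); alpha: 0.05; Power: 0.95" and "number of groups: 2; number of measurements: 3; total sample size: 32, that is, 16 per condition". Then f = sqrt(0.08/0.92) = 0.295. For the Group x Time test, lambda = f² x N x m/(1 - rho). The article gives neither the correlation nor the sphericity correction; I assume rho = 0.5 and epsilon = 1. With N = 32 and m = 3, lambda = 0.087 x 32 x 3/0.5 = 16.7 on 2 and 60 df, and power is 0.955. So 32 is reproduced. At 50 doctors ("To counterbalance possible drop-out, we assess 25 participants per condition") the same inputs give power 0.997. With rho = 0.3 or 0.7 the formula asks for 44 or 20.

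**Adding the survey score to the planned ANOVA.** Let S be the survey score, B the start-of-intervention score and Y the week-6 score, all with unit SD. With equal correlations rho, conditioning on S subtracts the same constant, rho², from every variance and covariance of the trial scores. A contrast between time points removes a constant. At rho = 0.5 the variance of Y - B is 2(1 - rho) = 1.00 with S in the model and 1.00 without it. Nothing is gained and a coefficient is spent.

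**Adding it to a baseline-adjusted model.** The residual variance of Y given B is 1 - r_BY². Adding S removes a further (r_SY - r_SB x r_BY)²/(1 - r_SB²). Estimating one more coefficient multiplies the variance of the group difference by about (n - 4)/(n - 5): 46/45 = 1.022 at n = 50 and 28/27 = 1.037 at n = 32.

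Scores not used for selection, n = 50 (correlations assumed; the article gives none):

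| r_SB, r_BY, r_SY | Residual variance, B only | B and S | Reduction before cost | After cost | 50 doctors act like |
|---|---|---|---|---|---|
| 0.5, 0.5, 0.5 | 0.750 | 0.667 | 11.1% | 9.1% | 55.0 |
| 0.6, 0.6, 0.6 | 0.640 | 0.550 | 14.1% | 12.2% | 56.9 |
| 0.7, 0.7, 0.7 | 0.510 | 0.424 | 17.0% | 15.1% | 58.9 |
| 0.6, 0.6, 0.5 | 0.640 | 0.609 | 4.8% | 2.7% | 51.4 |
| 0.6, 0.7, 0.5 | 0.510 | 0.500 | 2.0% | -0.2% | 49.9 |
| 0.6, 0.6, 0.36 | 0.640 | 0.640 | 0% | -2.2% | 48.9 |

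Worked line: for 0.6, 0.6, 0.5, (0.5 - 0.36)²/0.64 = 0.0306 and 0.0306/0.640 = 4.8%; then 1 - 0.952 x 1.022 = 2.7%. Simulated trials of 50 agree to within about one percentage point, giving 9 to 16% for the three equal-correlation rows.

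**The ISI.** Entry requires a survey ISI above 8, which truncates S. If a share p lies above the cut, c is the normal quantile at 1 - p and h = phi(c)/p, then the variance of S among entrants is 1 + c x h - h²: 0.265 for p = 30%, 0.410 for 58% and 0.493 for 70%. The 58% is the pooled active-duty prevalence cited in section 1.2; the others are assumed. Reduction after cost, n = 50:

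| r_SB, r_BY, r_SY | p = 30% | p = 58% | p = 70% |
|---|---|---|---|
| 0.5, 0.5, 0.5 | 2% | 4% | 5% |
| 0.6, 0.6, 0.6 | 3% | 6% | 7% |
| 0.7, 0.7, 0.7 | 6% | 9% | 10% |
| 0.6, 0.6, 0.5 | 0% | 0% | 1% |
| 0.6, 0.6, 0.36 | -2% | -2% | -2% |

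**The larger step.** Moving from change (variance 1.00 at rho = 0.5) to adjustment for the existing baseline (0.75) already saves 25%. The survey score is a further gain on top of that.

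**The case against.** The strongest reply is that the protocol makes no error here. Leaving out an optional second covariate contradicts nothing, and covariates are often settled in the analysis plan. The first half stands: this is a choice that could be better. The second half carries less weight, because section 2.8.1 itself fixes the model, the time levels and the list of variables to consider.

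The second reply is that the gain is small and uncertain for the primary insomnia outcome. This also stands. The ISI and the sleep continuity items cover only the last two weeks (section 2.5.1.2), and survey and baseline may be months apart, so the survey score may well correlate less with week 6 than the baseline does. In the faster-decaying cases above, the gain is nil or slightly negative.

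Third, the score is not a single number. Section 2.5.1 provides one questionnaire for private/civil life and one for military deployment, so a covariate must name its version.

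A reader might infer three stronger things. One is that the survey score is thrown away: it is not, since it decides eligibility and is described. Another is that precision is given up at no cost for every outcome: the extra coefficient has a cost, and for the ISI this can cancel the gain. The third is that the trial is too small or its sample size wrong: this point gives no support for that, because 32 is reproduced at an assumed correlation of 0.5 and the plan recruits 50.

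**Conclusion.** The point holds as an optional, cheap efficiency improvement. Everyone randomised has a pre-randomisation score on the primary sleep scales and the shared well-being scales, and section 2.8.1 leaves it out of both model and confounder list. In a baseline-adjusted model of 50 doctors, under equal or mildly decaying correlations of 0.5 to 0.7, using it would lower the variance of the group difference by about 3 to 15% for scores not used for selection. That is worth about 1 to 9 extra doctors. For the ISI the range is about -2% to +10%, mostly 0 to 6%. If the survey score adds nothing, the loss is about 2% at n = 50 and 4% at n = 32.

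These sizes rest on assumed correlations and an assumed share above the cut. One caveat concerns the well-being scales: section 2.3 and the Discussion mention poor well-being beside the ISI when describing who enters, without a cut-off. If well-being scores are also used for selection, their gain moves towards the ISI figures.

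**What to change.** In section 2.8.1:

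- Analyse weeks 3 and 6 in a model that adjusts for the start-of-intervention score. For scales not measured at week 3 (coping, emotion regulation, concentration, social activity, SDQ, mental toughness), analyse week 6 alone.
- Prespecify the Survey-Study 1 score of the same scale, in the same context version (private/civil or military), as a second covariate with its own coefficient at each post-baseline visit. Do this mainly for the shared secondary well-being scales, and optionally for the primary sleep outcomes.
- Keep a single baseline for the four scales added only for the trial.
- Do not simply add the survey score to the ANOVA that has baseline as a level of Time.

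No new data are needed. The change replaces the model rather than adding a term to it, and costs one coefficient per post-baseline visit: two where week 3 is measured, one otherwise. It should be fixed before outcome data are seen, because a covariate chosen afterwards would weaken the credibility of the result.

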### Intervention-study 2; study design

2.4

Medical doctors reporting sleep disturbances (see above) are contacted and invited to participate at the intervention of eCBTi. They are informed about the study design, the aims of the intervention study, the coded data handling, along with the information that participation or non-participation will have no advantages or disadvantages for their military career. Next, participants are randomly assigned either to the eCBTi condition (see details below) or to the ACC (see details below). All participants complete a series of self-rating questionnaires (see details below) at baseline, at week 3 (half time) and at week 6 (study end). At the end of the intervention, participants in the ACC can switch to the eCBTi condition.

### Measures

2.5

Survey-Study 1: Table 1 provides the overview of the study measures. The primary outcome measures are sleep disturbances (insomnia; sleep onset latency (SOL); awakenings after sleep onset (WASO) = disrupted sleep continuity). Secondary outcomes are psychological ill-being and well-being, including depression, anxiety, stress, coping strategies, emotion regulation, concentration, social activity, strengths and difficulties, and mental toughness.

Intervention-Study 2: Table 2 provides the overview of the study measures. Primary outcomes are change in sleep disturbances (insomnia; disrupted sleep continuity). Secondary outcomes are psychological ill-being and well-being, including the dimensions metioned above, and additionally: Sleep-related cognitions, experiential avoidance, and mindfulness self-awareness (see also Table 1).

**Table 2 tab2:** Elements of electronically delivered cognitive behavioral therapy for insomnia (eCBTi).

Session	Content
One	What is sleep? Provides an overview of the course and introduces the concepts of sleep, CBT, and insomnia.
Two	How various sleep habits impact on sleep. Provides stimulus control instructions, such as activities that are permitted or disallowed when in bed, daytime napping and what to do if sleep is not attained at night. Provides sleep restriction instructions, including setting specific bedtime, maintaining the same wake time, and restricting time spent in bed awake.
Three	Sleep hygiene education and discusses behavioral health practices, such as caffeine, alcohol, exercise, diet, smoking, and environmental factors’ impacts on sleep. Overview of relaxation techniques that support sleep.
Four	Role of automatic and negative thoughts and how they influence feelings. Identification of negative thoughts and alternative interpretations (cognitive restructuring)
Five	As session four; cognitive restructuring
Six	Review; summary of the main concepts of CBTi; what did I learn?

CBTi, cognitive behavioral therapy for insomnia.

#### Online survey

2.5.1

Please consider that there will be a questionnaire for private/civil life and one for military deployment.

##### Sociodemographic and military-related information

2.5.1.1

Participants report on their age, sex at birth, current job position (residency status; specialty; position within a hospital or extra-hospital activity); current military ranking and duration of military service (years).

##### Sleep

2.5.1.2

To assess sleep dimensions, three questionnaires are used.

###### Insomnia

2.5.1.2.1

Participants complete the German version (116) of the Insomnia Severity Index [ISI; (117)]. The questionnaire consists of seven items that assess difficulty falling asleep, sleeping without interruption, feeling refreshed in the morning, and daytime performance, in the last 2 weeks. Participants rate how well each item describes themselves from: 0 (= not at all) to 4 (= almost always), with higher sum scores reflecting a higher degree of insomnia.

###### Sleep continuity

2.5.1.2.2

To assess sleep continuity of the last 2 weeks, participants will be administered the modified Pittsburgh Sleep Quality Inventory (PSQI (118):). The questionnaire assesses usual bedtime, sleep onset latency, the number of awakenings after sleep onset, and wake-up time.

###### Sleep-influencing factors and rituals

2.5.1.2.3

The self-administered questionnaire evaluates working and sleep time, factors influencing sleep such as pets, children, on-call service, co-sleeping, noise and similar. Typical pre-sleep rituals are reading books, physical activity, texting/messaging, using tablets or similar electronic devices, sex, substances such as alcohol, cannabis, medications. Items are answered “yes” (scored as 1) or “no” (scored as 0.), with higher sum scores reflecting more unfavorable sleep-influencing factors.

##### Physical activity

2.5.1.3

Participants complete the 7-item International Physical Activity Questionnaire-Short Form (119) to assess weekly sedentary life style, and light to moderate and vigorous physical activity patterns. An overall total physical activity MET-minutes/week score will be calculated, and according to the amount of physical activity the subjects will enter the category of low, moderate or high physical activity.

##### Depression

2.5.1.4

To assess symptoms of depression, participants will be asked to complete the PHQ-9 (122), a brief depression severity measure; higher overall summed scores indicate higher symptoms of depression (0–4 points indicate no depression, 5–9 mild depression, 10–14 moderate depression, 15–19 moderatly severe and 20–27 severe depression).

##### Coping strategies

2.5.1.5

To assess coping strategies, participants will be administered the short-form of the Stressverarbeitungsfragebogen 120 [Coping with stress questionnaire] (121). Favorable coping strategies are: Minimizing and trivializing, self-instructions, active problem solving. Unfavorable coping strategies are: Social withdrawal, catastrophizing, substance use. Higher summed scores reflect more pronounced favorable and unfavorable coping strategies.

##### Depression, anxiety, stress

2.5.1.6

Participants will complete the Depression, Anxiety, Stress-questionnaire [DASS-21; (123, 124)]. Higher summed scores indicate a higher degree of depression, anxiety and stress.

##### Emotion regulation

2.5.1.7

Participants will complete the Emotion Regulation Questionnaire (125), which focuses on cognitive reappraisal and emotion suppression. Item scores will be summed to create a total score; higher overall scores indicate more cognitive reappraisal and more emotion suppression.

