##### Experiential avoidance

2.5.2.3

Participants will be administered the Experiential Avoidance Questionnaire [Hayes et al. (99, 137)]. It consists of 10 items, and typical items include: “I am afraid of my feelings.” or “My thoughts and feelings mess up my life.” Answers are given on 7-point Likert scales ranging from 1 (= never) to 7 (= always). Higher sum scores reflect a higher degree to accept also unpleasant experiences (emotions, cognitions), and accordingly, a lower degree of avoidance.

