We expect that compared to individuals in the ACC, and compared to the baseline, at the end of the intervention, individuals in the eCBTi condition report improved sleep disturbances, including dysfunctional cognitions impairing sleep, along with improvements for symptoms of depression, anxiety, coping with stress, emotion regulation, concentration, social activity, strength and difficulties, and mental toughness, and with improvements for experiential avoidance and mindfulness self-awareness. The intervention study should also help to understand possible improvements in sleep disturbances and psychological well-being both in the professional/private and in the military context.

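### The single emotion regulation total mixes reappraisal with suppression and has no defined direction of improvement; the stated direction of the experiential avoidance score conflicts with its quoted items unless they are reverse-keyed

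*Protocol article*

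**What the plan says.** **Emotion regulation.** Section 2.5.1.7 introduces a questionnaire "which focuses on cognitive reappraisal and emotion suppression" and then fixes the score: "Item scores will be summed to create a total score; higher overall scores indicate more cognitive reappraisal and more emotion suppression". No subscale scores are mentioned. Section 2.5 makes emotion regulation a secondary outcome in both studies. Section 2.8 includes it in the survey's correlations. Section 3.1.1 lists it among the dimensions expected to improve under eCBTi, without saying what improvement means for either strategy. Table 2 gives sessions four and five of eCBTi to cognitive restructuring, including alternative interpretations of negative thoughts.

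**Experiential avoidance.** Section 2.5.2.3 describes ten items rated from 1 (never) to 7 (always). It quotes two of them: "I am afraid of my feelings" and "My thoughts and feelings mess up my life". The direction of the sum is then stated: "Higher sum scores reflect a higher degree to accept also unpleasant experiences (emotions, cognitions), and accordingly, a lower degree of avoidance". Reverse-coding is not mentioned. The scale is an additional questionnaire of the intervention study only (Table 1; section 2.5.2) and a secondary outcome there. Section 3.1.1 expects a benefit, "and with improvements for experiential avoidance and mindfulness self-awareness", without giving a sign.

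**The concern.** The emotion regulation total is said to measure more of two different strategies at once. The treatment works on one of them, and nothing in the article says that the other should rise with it. A change in the total therefore cannot be attributed to either strategy or called better or worse. The same holds in the survey, where a correlation between the total and insomnia blends two correlations that may differ.

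For experiential avoidance, someone who often fears their feelings scores high on the items shown, yet the article reads a high sum as acceptance. If the items are summed as answered, the published interpretation could be the opposite of what happened. In both cases, if the meaning of the score is settled only after the data are seen, the direction of a declared outcome becomes a post-hoc choice.

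**Working it through.** The article gives no figure for this point, so the sizes below are illustrations with the assumptions stated.

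**1. Emotion regulation total**

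Let dR and dS be the treatment effects on reappraisal and suppression in SD units, a and b the subscale SDs, and r their correlation. The standardised effect on the sum is

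d_total = (a·dR + b·dS) / √(a² + b² + 2ab·r).

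The article gives none of these inputs. With a = b and r = 0 the denominator is √2 = 1.414 (in units of the common SD):

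| dR | dS | d_total |
|---|---|---|
| +0.5 | 0 | 0.5/1.414 = 0.35 |
| +0.5 | −0.25 | 0.25/1.414 = 0.18 |
| +0.5 | −0.5 | 0 |
| +0.25 | −0.5 | −0.25/1.414 = −0.18 |
| +0.5 | +0.5 | 1.0/1.414 = 0.71 |

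The last row shows that the total looks best when both strategies rise. It cannot tell that case from a larger gain in reappraisal alone.

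*Sensitivity.* With equal SDs and suppression unchanged, d_total runs from 0.40 (r = −0.2) to 0.29 (r = 0.5). With a/b = 1.5, the +0.5/−0.5 case gives 0.25/√(3.25 + 3r), that is 0.15 at r = −0.2 and 0.12 at r = 0.5. Offsetting is then partial, not complete.

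*Power.* Take a simple two-group comparison at the 25 per condition of section 2.7, before any drop-out, with two-sided alpha 0.05: power ≈ Φ(|d|·√(25/2) − 1.96).

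- Reappraisal alone, d = 0.5: Φ(1.77 − 1.96) = 42%.
- Total, suppression unchanged, d = 0.354: Φ(1.25 − 1.96) = 24%.
- Total, suppression −0.25, d = 0.177: Φ(0.63 − 1.96) = 9%.

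This is simpler than the planned repeated-measures ANOVA and serves only to compare the two ways of scoring.

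**2. Experiential avoidance sum**

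Ten items scored 1 to 7 give a plain sum from 10 to 70. Frequent agreement with either quoted item raises it. Suppose treatment improves every item by 0.5 points, and q of the ten items are worded toward acceptance. Without re-keying, the sum moves by 0.5·(q − (10 − q)) = q − 5. With the distress items reversed (8 − x), it moves by +5 whatever q is.

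- q = 0 (all items like the two quoted): −5.
- q = 5: 0.
- q = 8 (the most possible, since two distress items are shown): +3.

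So a plain sum gives a reversed, lost or diluted effect, depending on eight items that are not shown. If all ten are worded like the two quoted, the F test and its p-value are unchanged and only the interpretation is wrong. If wording is mixed, the size of the effect and the test change too.

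**3. Comparison with neighbouring scales**

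Sections 2.5.2.1 (beliefs about sleep), 2.5.2.2 (bedtime procrastination) and 2.5.2.4 (mindfulness) also quote items. In each, the stated direction fits the wording. Section 2.5.2.3 is the exception.

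**The case against.** The strongest reply is that this is a condensed article. None of its scale descriptions mentions reverse-coding, so silence in section 2.5.2.3 does not show that the step will be skipped. The intended direction is stated, and it can hold once distress-worded items are reversed. Only two of ten items are visible, and the keying may stand in the full protocol. This argument stands and makes the second part conditional. It does not remove the conflict between the items, response scale and direction as printed.

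For emotion regulation, the reply is that the wording is shorthand. Sections 2.5.1.5 (coping) and 2.5.1.6 (DASS-21) also describe summed scores over several dimensions, and separate scores are the natural reading there. That is weaker here, because section 2.5.1.7 expressly creates one total and then interprets it.

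Three stronger readings are tempting, and the documents do not support them.

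- *Effects will cancel or change sign.* Cancellation needs suppression to fall, which the article never predicts, and it is exact only for equal and opposite raw changes. Reversal of the avoidance score needs the absence of re-keying.
- *Survey correlations will have the wrong sign.* Experiential avoidance is not measured in the survey. The emotion regulation total makes a correlation hard to interpret, which is a different fault.
- *The sleep-influencing sum (section 2.5.1.2.3) is mis-scored.* A reader might infer this from "with higher sum scores reflecting more unfavorable sleep-influencing factors", since reading and physical activity are among the listed rituals. The text does not say how each item is keyed or which items enter the sum. The sum is also absent from Table 1, the outcome lists and the analytical plan.

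**Conclusion.** The emotion regulation rule is wrong as written. It fixes a single total that cannot separate two strategies and gives it no direction of improvement, although improvement is expected. A 0.5 SD reappraisal effect shrinks to about 0.35 SD if suppression does not move (equal SDs, r = 0; 0.29 to 0.40 for r from 0.5 to −0.2). It shrinks further, possibly to nothing, if suppression falls. If both strategies rise nothing cancels, but the total still cannot be interpreted.

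The experiential avoidance sentence contradicts its own sample items unless they are reverse-keyed. The consequence is conditional: a reversed interpretation with uniform wording, or a diluted effect with mixed wording.

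Both scales are secondary outcomes. The primary outcomes (insomnia and sleep continuity) and the sample size of section 2.7 are untouched. The correction should still be made before the data are analysed, because it is cheap and fixes the meaning of two declared outcomes.

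**What to change.** - **Section 2.5.1.7:** score cognitive reappraisal and emotion suppression as two separate subscales, drop the total, and state for each which direction counts as improvement. Carry the two scores through the survey correlations and regressions (section 2.8) and the Group × Time analyses (section 2.8.1), and name them in section 3.1.1.
- **Section 2.5.2.3:** either list the items that are reverse-coded before summing, so that a higher sum does mean more acceptance, or correct the sentence to say that a higher sum means more avoidance. Give section 3.1.1 the matching sign.

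The cost is a few sentences and one extra secondary variable, which joins the existing Bonferroni-Holm correction wherever emotion regulation is already included. No additional data or participants are needed, because the item responses are collected in any case.
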